# Prophylactic perioperative cefuroxime levels in plasma and adipose tissue at the time of caesarean section (C-LACE): a protocol for a pilot experimental, prospective study with non-probability sampling to determine interpatient variability

**DOI:** 10.1186/s40814-021-00794-3

**Published:** 2021-02-18

**Keywords:** Caesarean section, Cefuroxime, Pharmacokinetics, Obese, Pregnant women, Surgical site infection

## Abstract

**Background:**

The aim of the C-LACE study is to measure cefuroxime concentration in plasma and adipose tissue of non-obese and obese pregnant women undergoing caesarean section.

**Methods:**

This study plans to compare maternal cefuroxime concentrations (plasma and adipose tissue), at the time of skin incision and time of skin closure during a caesarean section from non-obese (body mass index BMI < 30 kg/m^2^) and obese (BMI ≥ 30 kg/m^2^) pregnant women. The incidence of post-surgical site infection will also be measured. At least 15 participants are required for each arm (non-obese vs obese) with a total of 30 participants. The study participants will be followed up between 30 and 40 days post-caesarean section to record details of any post-caesarean surgical infection to explore correlations between BMI, measured cefuroxime concentrations and post-caesarean infection rates.

**Discussion:**

This pilot study will allow the development of a model testing the inter-patient variability in plasma and adipose tissue concentrations of cefuroxime. The results will facilitate the development of a larger study to determine whether differences in cefuroxime plasma and tissue concentration in obese and non-obese women can support the development of a physiologically based pharmacokinetic model. This model can then be used to propose dosing adjustments that can be used in a further trial to optimise cefuroxime dosing for women undergoing caesarean section.

**Trial registration:**

ISRCTN Registry, ISRCTN17527512. Registered on 26 October 2020

**Supplementary Information:**

The online version contains supplementary material available at 10.1186/s40814-021-00794-3.

## Administrative information

This protocol follows the SPIRIT checklist (items of the checklist are numbered in curly brackets).

## Background {6a}

The prevalence of obesity in pregnant women in England at the time of booking a caesarean section (CS) has been reported to be 16% [1, 2]. One complication of obesity in pregnancy relates to the requirement for operative delivery, i.e. CS. The rate of CS in an obese (Body Mass Index BMI ≥ 30 kg/m^2^) pregnant population is 33.8% [3]. The rate of post-CS infection is higher amongst obese pregnant women compared to those who are not obese; the adjusted odds ratio of surgical site infection in an obese population was reported to be 2.41 (95% CI 1.73–3.37) [4]. Prophylactic single dose perioperative intravenous (IV) antibiotic is recommended for CS; and several studies have examined the use of alternative antibiotics, with cefazolin being the most commonly used in the USA and cefuroxime in the UK. Numerous studies have focussed on the use of cefazolin in obese patients undergoing CS to gain an understanding of optimal dosing and clinical outcomes [5]. Several studies proposed an increased dose of cefazolin (3 g) compared to the standard dose (2 g) for obese pregnant women to achieve sufficient antibiotic levels during CS [6–8]. It was postulated by Holt et al. (in 1994) that doses of cefuroxime up to 1500 mg may not achieve sufficient minimum inhibitory concentration (MIC) for most of the common bacteria in maternal blood during CS [9]. Sub-therapeutic antibiotic concentration is a crucial factor in global bacterial resistance. It is essential that the therapeutic concentration of antibiotic is achieved in both maternal blood and at the site of incision during CS for effective therapy. No study to date has measured cefuroxime concentrations in blood and adipose tissue in obese pregnant women undergoing CS [10]. Thus, a study to explore the drug concentration in this population at the time of CS is essential. This study will analyse cefuroxime concentration in plasma and adipose tissue samples to accurately measure levels achieved in non-obese and obese pregnant women undergoing CS to confirm if therapeutical cefuroxime levels are reached in plasma and adipose tissue. Further, to use the measured cefuroxime concentrations to verify a physiologically based pharmacokinetic (PBPK) model of cefuroxime in CS to explore the impact of (i) dose and (ii) BMI post-administration of cefuroxime on both blood and tissue cefuroxime concentrations in an obese population and suggest a dose adjustment if required and applicable.

### Objectives {7}

The main objective of conducting this pilot and feasibility study is to assess the process and protocol of recruiting patients, sample collection, follow-up and procedure of C-LACE. Also to gain an understanding of cefuroxime concentrations in normal-body weight pregnant vs. obese pregnant women. The primary objective is to measure the concentration of cefuroxime in the collected blood and tissue samples using an appropriate analytical method and to assess whether cefuroxime administered provides concentrations above the MIC in both the blood and adipose tissue for all patients regardless of their BMI. Additionally, to assess whether there are differences in cefuroxime concentrations from obese vs non-obese women.

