### Part A: Cefuroxime levels in plasma and adipose tissue

The minimum inhibitory concentration is not harmonised between guidelines; thus, the time above the minimum inhibitory concentration (T>MIC) will be reported for MIC values of 1, 4 and 8 mg/L [5, 11] as these values correlate to the most common bacteria involves in post-CS surgical infections (Table 1).

**Table 1 Tab1:** Most common bacteria causative of infection post-caesarean section and the minimum inhibitory concentration range/breakpoint

	Microorganism	MIC range/breakpoint (mg/L) [5, 11–13]
Gram-negative bacteria	*Escherichia coli*	0.001–8
	*Haemophilus influenzae*	2
	*Klebsiella oxytoca*	8
	*Proteus mirabilis*	0.001–8
	*Ureaplasma urealyticum*	ND
Gram-positive bacteria	*Enterococcus faecalis*	ND
	*Staphylococcus aureus*	4
	*Staphylococcus epidermidis*	0.25–4
	*Streptococcus pneumoniae*	1
Other organisms	*Raoultella ornithinolytica*	0.001–8
	*Morganella morganii*	ND

*ND* Not determined

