### Participant selection and enrolment

Any patient (18–50 years) who requires a CS as part of their clinical care will be screened for inclusion. The potential participants will be identified using hospital clinical lists, where lists relate to a pre-booked CS a Good Clinical Practice (GCP) trained research midwife who is a member of the clinical care team will assess the eligibility of patients to participate in the study according to inclusion/exclusion criteria using screening form. The woman will then be provided with the participant information sheet at this meeting by the research midwife. In addition, if a pregnant woman is booked for CS at a meeting they may be informed about the study by a research midwife or their clinical care team and provided with a participant information sheet. The participants will receive information about the study well in advance (at prior clinic appointments) and at least 24 hours prior to CS so that all participants have sufficient time to consider taking part.

This study plans to compare data from obese (BMI ≥ 30 kg/m^2^) and non-obese women (BMI < 30 kg/m^2^) at the time of booking (10–14 weeks of pregnancy). At least 15 participants are required for each arm with a total of 30 participants. The study sequence is summarised in Table 2.

**Table 2 Tab2:** Summary of the C-LACE study sequence and methodology

Timing	Activity
Caesarean section booking clinic	Clinic list will be reviewed for eligible participants using the screening form
On the day of caesarean section	A Venflon cannula will be inserted into the woman as part of the research process to enable withdrawal of the required blood samples without the need for additional needles. This second access point will ensure that the blood sampling is minimally disruptive to the CS procedure.
At 30–40 days post-caesarean section	Participant’s medical file and notes will be reviewed by the research midwife to identify any post-surgical site infection which will be recorded on the 6-week outcome form. Research midwife will attempt to contact the participant 3 times between 30 and 40 days post-CS to complete the follow-up interview form.
Samples analysis	Blood and adipose tissue will be analysed by LC-MS/MS [15]

*GCP* Good Clinical Practice, *CS* Caesarean section, *LC-MS/MS* liquid Chromatography with tandem mass spectrometry

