### Statistics {20a}, sample size {14} and study assessment

There is no predefined sample size yet sufficient numbers are required to provide an estimate of average values as well as the level of inter-patient variability. Previous work to measure the concentration of antibiotics in plasma and in tissue in obese and non-obese pregnant women following CS has used sample sizes of 14 in each arm to detect differences in adipose antibiotic concentration [16, 17]. Therefore, in this study, we plan to recruit 15 women in each arm (BMI < 30 kg/m^2^ and BMI ≥ 30 kg/m^2^). The BMI measurements will be taken from the women at their time of booking appointment which occurs between 10 and 14 weeks of pregnancy. The BMI of participants immediately prior to CS will be determined to review any major changes during their pregnancy which may affect the results, for example, a change from < 30 kg/m^2^ to an extremely obese participant at CS.

The differences in mean concentration values in plasma and adipose tissue between the obese and non-obese populations will be compared using ANOVA analysis to determine whether there are significant differences. SPSS software will be used for all statistical analysis. The rate and type of infection will be analysed. The rate of infections will be analysed in correlation with (1) dose administered, (2) BMI and (3) cefuroxime concentrations at both sites at the time of skin incision and skin closure.

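### Read literally, the primary objective asks an all-or-none question about the MIC that 15 women per arm cannot settle and that the stated ANOVA on means does not address

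*Protocol article*

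**What the plan says.** The Objectives section {7} of the protocol article first gives a main objective about feasibility. It then names a primary objective: to measure cefuroxime in the samples and "to assess whether cefuroxime administered provides concentrations above the MIC in both the blood and adipose tissue for all patients regardless of their BMI". The Background {6a} puts the same question as measuring levels "to confirm if therapeutical cefuroxime levels are reached in plasma and adipose tissue".

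The statistics and sample size section says "There is no predefined sample size yet sufficient numbers are required to provide an estimate of average values" and the level of inter-patient variability. It cites earlier work that "has used sample sizes of 14 in each arm to detect differences in adipose antibiotic concentration", and concludes that "in this study, we plan to recruit 15 women in each arm". Participant selection and enrolment gives the same number: "At least 15 participants are required for each arm with a total of 30 participants".

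For the concentrations, the comparison stated is this: "The differences in mean concentration values in plasma and adipose tissue between the obese and non-obese populations will be compared using ANOVA analysis". Part A of the outcomes says that time above the MIC "will be reported for MIC values of 1, 4 and 8 mg/L". The objective itself speaks of the MIC in the singular and does not say which of the three is meant.

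**The concern.** An objective that covers every patient has only two literal answers. It is yes if no woman is below the MIC and no if one woman is. Neither answer says much about how often women in each BMI group are under-exposed, which is what a reader wants to know. With 15 women, finding none below is compatible with a sizeable true share below, and one below is compatible with very high attainment.

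The stated ANOVA does not fill the gap. It asks whether mean concentrations differ between the arms. If both arms had the same distribution, with the same sizeable share of women below the MIC, the ANOVA would have no difference to find.

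The obese arm matters most. It is the reason for the study, and the results are meant to feed a pharmacokinetic model, a larger study and possible dosing proposals. A clean result in 15 obese women could be carried forward as stronger evidence than it is.

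**Working it through.** **The plan's own figure.** The article states 15 per arm and 30 in total. It gives no significance level, power, effect size, standard deviation or target precision, so 15 cannot be reproduced by formula. It follows a precedent of 14 per arm. That precedent concerns differences in adipose concentration, not the share of women above a threshold.

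**Inputs.**
- n = 15 per arm and 30 overall (statistics section; Participant selection and enrolment).
- n = 12 as a lower case. The feasibility criteria accept complete sampling in at least 75% of each arm; 0.75 × 15 = 11.25, so 12 women meet it.
- A 95% confidence level. This is an assumption, because the article names none; both the one-sided and two-sided conventions are shown.

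**No woman below the MIC.** If 0 of n women are below, the exact upper limit for the true share below is 1 − 0.05^(1/n) one-sided and 1 − 0.025^(1/n) two-sided.

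| Result | One-sided 95% | Two-sided 95% |
|---|---|---|
| 0 of 15 below | 1 − 0.05^(1/15) = 18.1% | 1 − 0.025^(1/15) = 21.8% |
| 0 of 12 below | 22.1% | 26.5% |
| 0 of 30 below (arms pooled) | 9.5% | 11.6% |

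For 0 of 15, the rule of three (3/15 = 20.0%) and the two-sided Wilson limit (20.4%) agree. The largest two-sided lower limit for the share above at n = 15 is 0.025^(1/15) = 78.2%.

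**One woman below the MIC.** With 1 of 15 below, the exact upper limit is 27.9% one-sided and 31.9% two-sided. The two-sided lower limit is 1 − 0.975^(1/15) = 0.2%. The two-sided interval moves from 0–21.8% to 0.2–31.9%. The two overlap heavily, yet the literal answer flips from yes to no.

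**How often each literal answer would arise.** The true rates here are assumed for illustration; the article gives none.
- True share below 5%: all 15 above with probability 0.95^15 = 46%.
- True share below 10%: 0.90^15 = 21%.
- True share below 20%: 0.80^15 = 3.5%.
- True share below 2% in both arms, one matrix and one time: at least one of 30 below with probability 1 − 0.98^30 = 45%.

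**Which MIC.** The thresholds are 1, 4 and 8 mg/L. A woman can be above one and below another, so even the literal yes or no can differ by threshold.

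**The case against.** The strongest reply is that the article contains no all-or-none decision rule. The objective is to assess whether, and the Background asks to confirm if, not to confirm that. The stated success criteria cover recruitment, sampling, assay, form completion and retention; none concerns MIC attainment. The words about all patients regardless of BMI can also be taken to mean across both BMI groups. The study is a pilot sized to estimate averages and variability, and its results go to a model, a larger study and a further trial. Part A also plans to report time above three MIC values, so the MIC question is not ignored. Finally, interval methods for proportions are often left to the full protocol or the analysis plan.

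Most of this stands. A reader might infer that 15 of 15 above the MIC would be declared adequate, or that one low value would be declared a failure. The article supports neither. The probabilities of 46%, 21% and 45% therefore show how poorly the literal question separates good from poor attainment; they are not error rates of a planned test. The absence of an interval from the article is not itself a fault.

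What remains is the published wording. The literal sense is a natural reading, and an interval supplied elsewhere would leave that question in place. The one comparison of concentrations that the article names is on means. Time above the MIC is a duration, not the share of women above each threshold at each sample.

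**Conclusion.** The point holds as a matter of wording and of fit between objective and analysis. Read literally, the primary objective cannot be settled with 15 women per arm, and the ANOVA on mean concentrations does not address it. A clean obese arm would leave up to 18.1% (one-sided) or 21.8% (two-sided) of such women possibly below the MIC. If only 12 were fully sampled, the limits would be 22.1% or 26.5%.

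These limits assume a 95% level, one threshold, matrix and time, and independent women who represent their group. The article describes non-probability sampling, so the last assumption is weak and the limits are best taken as the least uncertainty to admit.

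It does not follow that the plan would mislead by design, or that it needs a formal adequacy test. The objective is loosely worded for a pilot; the remedy is cheap and worth making.

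**What to change.** Restate the objective along these lines: *to estimate, in each BMI group, the proportion of women whose cefuroxime concentration exceeds 1, 4 and 8 mg/L, in plasma and in adipose tissue, at each sampling time, with exact 95% confidence intervals.* Drop the reference to all patients as the criterion.

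Add to the statistics section that these proportions address the MIC objective and the ANOVA addresses only the difference in means. Add also that 15 of 15 above a threshold does not exclude about 1 in 5 below it.

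Call the intervals exploratory, for two reasons: the design is a pilot with non-probability sampling, and the table is large (2 arms × 5 samples × 3 MIC values = 30 proportions). A test against a target proportion is not needed.

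The cost is a change of wording and one table from samples already planned; no participants or procedures are added. The downside is a less definite conclusion: at 15 per arm the two-sided lower limit for attainment cannot exceed about 78%, even with no woman below.

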### Trial design {8}

A single-centre experimental, prospective pilot study with non-probability sampling.

## Methods/design

### Aims and methodologies

To measure cefuroxime concentration in plasma and adipose tissue (within the incision) at time of skin incision and skin closure in obese and non-obese pregnant patients requiring CS. Moreover, to explore the relationship between the dose of cefuroxime administered and concentration measured in both blood and adipose tissue with respect to BMI of the patient. To measure the incidence of post-CS infections in obese and non-obese pregnant women at 30–40 days post-CS; and to assess if the rate of infection is correlated with BMI, dose administered and cefuroxime blood or adipose tissue concentrations.

Cefuroxime is administrated to pregnant women undergoing CS as per Birmingham Women’s Hospital protocol; i.e. IV infusion 30–60 min before skin incision.

### Outcomes {12}

Outcomes of C-LACE pilot and feasibility study are AS FOLLOWS:
Patients’ recruitment rateCollecting samples strategiesAnalytical method for sample analysisData collection and forms completionFollow-up and participants’ retention

### Part A: Cefuroxime levels in plasma and adipose tissue

The minimum inhibitory concentration is not harmonised between guidelines; thus, the time above the minimum inhibitory concentration (T>MIC) will be reported for MIC values of 1, 4 and 8 mg/L [5, 11] as these values correlate to the most common bacteria involves in post-CS surgical infections (Table 1).

**Table 1 Tab1:** Most common bacteria causative of infection post-caesarean section and the minimum inhibitory concentration range/breakpoint

	Microorganism	MIC range/breakpoint (mg/L) [5, 11–13]
Gram-negative bacteria	*Escherichia coli*	0.001–8
	*Haemophilus influenzae*	2
	*Klebsiella oxytoca*	8
	*Proteus mirabilis*	0.001–8
	*Ureaplasma urealyticum*	ND
Gram-positive bacteria	*Enterococcus faecalis*	ND
	*Staphylococcus aureus*	4
	*Staphylococcus epidermidis*	0.25–4
	*Streptococcus pneumoniae*	1
Other organisms	*Raoultella ornithinolytica*	0.001–8
	*Morganella morganii*	ND

*ND* Not determined

### Part B: Surgical site infection

The rate of surgical site infection will be reported in non-obese and obese pregnant women undergoing CS. This study will follow the definition of surgical infection as per the definitions set out by the US Centre’s for Disease Control and Prevention (Centre’s for Disease Control and Prevention 2019) [14].

### Target population

The target population are non-obese and obese pregnant women undergoing elective CS at Birmingham Women’s Hospital.

### Eligibility criteria {10}

#### Inclusion criteria

Pregnant women 18 to 50 years old, with a singleton pregnancy undergoing elective CS at 37 weeks or over.Participant is able to give consent and agree to sample storage.Participant agrees to be contacted for follow-up.Participant contributing to the study needs to be able to read and/or understand English.

#### Exclusion criteria

Multiple pregnancyPrevious CS that resulted in a surgical site infectionEmergency CSAny non-elective CS including those requiring early delivery without threat to maternal or foetal health that were not previously planned.Body mass index (BMI) less than 18 kg/m^2^ or greater than or equal to 45 kg/m^2^ (at time of first pregnancy appointment and at time of delivery).Currently enrolled in a randomized controlled trial for an intervention to reduce post-operative surgical site infectionDiabetes (type 1, type 2 or gestational)HypertensionRenal diseaseCardiovascular disease (e.g. maternal structural cardiac disease)Liver diseaseInflammatory bowel disease (e.g. Crohn’s disease or ulcerative colitis)Cephalosporin or penicillin allergyAdministration of antibiotic within 1 week prior to deliverySuspected pre-existing infection (including chorioamnionitis)Autoimmune disease (e.g. systemic lupus erythematosus, rheumatoid arthritis)Chronic use of corticosteroidHistory of wound breakdown in an abdominal surgeryPrior laparotomy for any indication (e.g. previous ovarian cystectomy or previous bowel surgery)

### Setting {9}

This single-centre study will take place at Birmingham Women’s Hospital which is a large teaching hospital that is part of Birmingham Women’s and Children’s Hospital NHS Foundation Trust.

### Participant selection and enrolment

Any patient (18–50 years) who requires a CS as part of their clinical care will be screened for inclusion. The potential participants will be identified using hospital clinical lists, where lists relate to a pre-booked CS a Good Clinical Practice (GCP) trained research midwife who is a member of the clinical care team will assess the eligibility of patients to participate in the study according to inclusion/exclusion criteria using screening form. The woman will then be provided with the participant information sheet at this meeting by the research midwife. In addition, if a pregnant woman is booked for CS at a meeting they may be informed about the study by a research midwife or their clinical care team and provided with a participant information sheet. The participants will receive information about the study well in advance (at prior clinic appointments) and at least 24 hours prior to CS so that all participants have sufficient time to consider taking part.

This study plans to compare data from obese (BMI ≥ 30 kg/m^2^) and non-obese women (BMI < 30 kg/m^2^) at the time of booking (10–14 weeks of pregnancy). At least 15 participants are required for each arm with a total of 30 participants. The study sequence is summarised in Table 2.

**Table 2 Tab2:** Summary of the C-LACE study sequence and methodology

Timing	Activity
Caesarean section booking clinic	Clinic list will be reviewed for eligible participants using the screening form
On the day of caesarean section	A Venflon cannula will be inserted into the woman as part of the research process to enable withdrawal of the required blood samples without the need for additional needles. This second access point will ensure that the blood sampling is minimally disruptive to the CS procedure.
At 30–40 days post-caesarean section	Participant’s medical file and notes will be reviewed by the research midwife to identify any post-surgical site infection which will be recorded on the 6-week outcome form. Research midwife will attempt to contact the participant 3 times between 30 and 40 days post-CS to complete the follow-up interview form.
Samples analysis	Blood and adipose tissue will be analysed by LC-MS/MS [15]

*GCP* Good Clinical Practice, *CS* Caesarean section, *LC-MS/MS* liquid Chromatography with tandem mass spectrometry

